**Results:**

The study will compare changes in primary and secondary outcome measures across the three treatment groups over time (baseline vs. week 8, month 3 and month 6) using appropriate statistical models for longitudinal data (e.g., repeated measures ANOVA, mixed-effects models.

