### Trial design and study setting

2.1

This study employs a naturalistic observational (non-randomization) design, conducted within real-world clinical settings for a six-month period (see **Figure 1**) where the group assignment reflects patient preference and clinical practice in specialized hospitals. The study population comprises 105 adult participants. Participants will be observed in one of three treatment groups, each consisting of approximately 35 individuals, based on the treatment they receive (see **Figure 1**).

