### Primary and secondary outcome measures

2.7

The primary endpoint will focus on changes in depressive symptom severity, measured using primary MADRS, and secondary HAM-D and PHQ-9 especially in week 8. The use of multiple scales enhances the reliability and validity of the assessment, providing a more comprehensive picture of symptom change. Several secondary outcome measures will exploratively elucidate the impact of treatments on various aspects of patient well-being and functioning. These include side effects (UKU, GASE, MARS), quality of life and daily functioning (WHOQoL-BREF, GAF, FAST) as well as general health measures (e.g. lab tests). This comprehensive approach ensures that the study captures a broad range of outcomes, providing a robust and nuanced evaluation of the treatment effect and side effects of allopathic and Ayurvedic treatments for MDD. The question is exploratory in nature due to the design and methodology.

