### Sample size calculation and statistical analysis

2.9

We hypothesise that all treatment groups lead to a statistically significant reduction in symptoms of depression between baseline and week 8 (within group effect). We also hypothesize that the groups do not differ in terms of treatment success (between group effect). We performed a power analysis to calculate the sample size. With a sample size of N = 105 patients, an alpha error probability of 0.5 and a moderate effect size (0.5) (for change in symptoms of depression), we achieve a statistical power of >0.8. An effect size of 0.5 equates to a mean difference in the MADRS score between baseline and week 8 of 50%, which reflects a commonly accepted clinical response measure in depression studies. In practise , this would mean a reduction of 15 points on the MADRS scale from 30 points at baseline to 15 points at week 8. Such a kind of reduction has been seen in other interventional studies in depression.

Data analysis will be conducted by the team at the Department of Psychiatry, University of Münster. The primary and secondary outcome measures will be analysed using an intention-to-treat (ITT) and exploratory approach. We will focus on specialized analyzation for longitudinal data. In addition, we will correct for confounding variables in all analyses where significant differences arise between the groups.

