The choice of statistical test will depend on the nature of the data and the specific research question. For continuous outcome variables (e.g., scores on depression rating scales, quality of life scores, continuous physiological measures), Analysis of Variance (ANOVA) or independent samples t-tests will be used to compare means between the three treatment groups (Ayurvedic-only, Allopathic-only, and Combination). *Post-hoc* tests (e.g., Tukey’s HSD, Bonferroni correction) will be employed if significant differences are found between groups to determine which specific groups differ significantly. For categorical outcome variables (e.g., presence or absence of adverse events, categorical measures of quality of life, treatment adherence categories), Chi-square tests or Fisher’s exact tests (for small sample sizes) will be used to compare proportions between treatment groups. Given the repeated measures design (baseline, 8 weeks, 3 months, 6 months), appropriate statistical models for longitudinal data (e.g., repeated measures ANOVA, mixed-effects models) will be used to analyse changes in outcome measures over time within each treatment group and to examine the interaction effects between treatment group and time. This will allow for a more powerful examination of treatment effects and the assessment of treatment response trajectories. Strategies to address missing data will be carefully considered and documented. In addition to p-values, effect sizes (e.g., Cohen’s d) and 95% confidence intervals will be reported for all significant findings. All statistical analyses will be performed using appropriate statistical software packages (e.g., SPSS, R).

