### Limitations

3.2

While the real-world study has advantages for translation and generalizability to clinical practice , this comes with limitations such as potential confounding, selection bias, and heterogeneity of Ayurvedic and allopathic interventions, which could affect internal validity. In this context, it should be noted that the choice of treatment depends strongly on the preferences of the patients and the approach of the treating clinic and physicians, even though participatory decision-making processes are particularly important with regard to the treatment of psychiatric patients. Even though a wait-list control condition or a no-intervention arm would provide valuable data and improve the interpretability of the findings, this would not be ethically justifiable in our sample.

Moreover, the generalizability is limited to comparable settings in India. It should be noted that the exclusion of suicidality and substance abuse leads to a small but ethically necessary restriction of the naturalistic cohort.

Furthermore, the approach of a multimodal and routine (non-randomised) intervention program in both Ayurvedic and allopathic treatment arms have the potential disadvantage that no causal inferences can be made about specific effects of individual components of the treatment. However, we would like to emphasize that a more holistic approach to treating depression reflects clinical reality and carries a higher weight for translation into routine settings.

This study is designed to determine whether the applied treatments are effective in producing changes in the dependent variables. However, it is not intended to explain how or through which mechanisms the treatment leads to successful outcomes. Addressing this question would require a research design that captures the complexity of real-world settings with greater ecological validity (e.g., alternative approaches such as the integrative single-case design) (41).

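### The three arms may be compared by independent t-tests with correction only afterwards, and the primary endpoint is not pinned to MADRS at week 8: about 12% instead of about 5% false between-arm differences on that route

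*Protocol article*

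**What the plan says.** All references are to the protocol article.

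- **Test between arms (section 2.9).** "Analysis of Variance (ANOVA) or independent samples t-tests will be used to compare means between the three treatment groups". The next sentence gives Tukey's HSD and Bonferroni as examples of post-hoc tests, to be used if the groups are found to differ. The same section also names repeated measures ANOVA and mixed-effects models for the longitudinal data.
- **Primary endpoint (section 2.7).** "The primary endpoint will focus on changes in depressive symptom severity, measured using primary MADRS, and secondary HAM-D and PHQ-9 especially in week 8".
- **Time points.** The abstract (Results) announces comparisons "across the three treatment groups over time (baseline vs. week 8, month 3 and month 6", and the treatment-effect objective in section 1.2 lists the same times. Both hypotheses in section 1.2 are set at week 8.
- **Between-arm hypothesis (section 2.9).** "We also hypothesize that the groups do not differ in terms of treatment success (between group effect". Section 1.2 words it for allopathic against Ayurvedic treatment, section 2.9 for the groups in general.
- **Level, power and size.** Section 2.9 gives "an alpha error probability of 0.5 and a moderate effect size (0.5" and then "we achieve a statistical power of >0.8". Section 2.1 describes "three treatment groups, each consisting of approximately 35 individuals".
- **Status.** Sections 1.2, 2.7 and 2.9 call the question or the analysis exploratory.
- **Reporting (section 2.9).** Effect sizes and 95% confidence intervals are promised only for significant results.

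**The concern.** An independent-samples t-test compares two means. Offering it as an alternative to ANOVA for three arms means three pairwise tests on each outcome. The correction comes after a difference has been found. That order suits ANOVA, where the global test guards the pairs. It does not guard the t-test route, where the first step is already the set of pairwise tests. The two routes can disagree on whether the arms differ, and the choice between them is left to the nature of the data.

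The loose endpoint sentence adds to this. MADRS is ranked first, but two secondary scales share its sentence, and the wording does not exclude later times from the primary endpoint. Section 2.1 lets participants re-evaluate their treatment at week 8, so a contrast at month 3 or 6 may answer a different question from one at week 8.

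What is at stake is a between-arm difference on depressive symptoms that arises by chance. The reverse also matters: because estimates are tied to significance, the result the authors expect (no difference) could appear without an interval.

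**Working it through.** **Inputs from the article.** Three arms of about 35 (section 2.1); effect size 0.5, power above 0.8 and printed alpha 0.5 (section 2.9); comparisons at week 8, month 3 and month 6 (abstract, section 1.2); one primary and two secondary depression scales (section 2.7).

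**Assumptions, not in the article.** Two-sided 0.05, no dropout, normal outcomes, and a range of correlations between time points and between scales.

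**Step 1: the plan's own power figure.** For a paired test within one arm the noncentrality is d × √n = 0.5 × √35 = 2.96 on 34 degrees of freedom. Power is 0.820 at alpha 0.05, which matches the stated figure. At the printed alpha of 0.5 the same test gives 0.989. For one pair of arms the noncentrality is d × √(n/2) = 0.5 × √17.5 = 2.09 on 68 degrees of freedom, and power at 0.05 is 0.54. The power statement therefore fits the within-arm question and does not describe a between-arm test on a pair.

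**Step 2: MADRS at week 8, no true difference.** If the three pairwise tests were independent, the chance of at least one p < 0.05 would be 1 − 0.95³ = 0.143. They share arms, so the true figure is lower. Simulation with three arms of 35 (10,000 runs) gives:

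| Route | At least one false difference |
|---|---|
| Three uncorrected t-tests | 12.2% |
| One ANOVA | 4.8% |
| ANOVA, then Tukey | 4.4% |

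The simulation standard error of the first figure is √(0.122 × 0.878 / 10,000) = 0.003, so the gap is not noise. The t-test route has about 2.5 times the ANOVA rate (12.2 / 4.8).

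**Step 3: MADRS at week 8, month 3 and month 6, all counted as deciding.** This makes 3 pairs × 3 times = 9 t-tests.

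| Correlation between times | t-tests | ANOVA | ANOVA, then Tukey |
|---|---|---|---|
| 0 | 33.0% | 14.5% | 13.0% |
| 0.5 | 28.2% | 12.5% | 11.5% |
| 0.9 | 19.8% | 8.4% | 7.8% |

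Even the ANOVA route exceeds 5% here, because no correction across times is stated. That is why the time point needs fixing as well as the test.

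**Step 4: the proposed remedy.** With one endpoint, one time and a global test followed by Tukey, the rate is the 4.4% of step 2. With one pre-named pair it is 5% by construction.

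**The case against.** The strongest reply is that the article already ranks most of this. MADRS is called primary, and HAM-D and PHQ-9 secondary, in the abstract, section 1.2 and section 2.7. Week 8 is the time point of both hypotheses in section 1.2 and of the power statement in section 2.9, and section 3.1 says that long-term effects are studied exploratively. ANOVA is allowed by the same sentence, correction between arms by the next, and longitudinal models are named too. The study presents itself as exploratory and hypothesis-generating.

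Much of this stands, and it rules out stronger readings:

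- A reader might infer that the plan's false-positive rate runs from 12% to more than half. It does not start at 12%, because the ANOVA route gives about 5%. The upper end needs all 3 × 3 × 3 = 27 tests to decide together, although two scales are labelled secondary. It also moves from 31% to 69% as the assumed correlations go from 0.9 to 0.
- A reader might infer that the arms will be compared without correction. That is only one reading of one branch. If every claim on the t-test route had to survive Bonferroni over the three pairs, the rate would stay at or below 5%. The text does not say that it must.
- A reader might infer that allopathic against Ayurvedic treatment has to be the single deciding pair. Section 1.2 points that way, but the wording in section 2.9 reads naturally as a three-arm question.
- A reader might cite section 3.2, "This study is designed to determine whether the applied treatments are effective in producing changes in the dependent variables", as proof of a confirmatory comparison of arms. It reads at least as well as change under treatment.

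What the reply does not remove is a test option that does not fit three groups and an endpoint sentence looser than the hypotheses it serves. An exploratory label does not repair either.

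**Conclusion.** The point holds in a limited form. On MADRS at week 8, the wording of section 2.9 allows a route with about a 12% chance of at least one false between-arm difference, beside a route with about 5%, and it leaves the choice open. The rate reaches roughly 20% to 33% only if MADRS at months 3 and 6 is also t-tested and treated as deciding, and that range depends on correlations that the article does not give.

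The figures assume a two-sided 0.05 level. The article prints 0.5, probably a slip, which should be corrected. They also assume 35 per arm, no dropout and exchangeable arms. The arms are not randomised, and the allopathic arm is treated at a different hospital from the other two, so the figures describe chance alone. Confounding comes on top, and no choice of test removes it.

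The change is worth making because it is cheap and specific. It does not undermine the study, given its exploratory status. Nor does it address the low power for a pair (0.54 at an effect of 0.5): a non-significant result would still not show that the arms are equally effective.

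**What to change.** 1. **Section 2.7 and abstract:** state MADRS change from baseline to week 8 as the only primary endpoint. Drop the qualifier before week 8, and move HAM-D, PHQ-9, month 3 and month 6 to secondary or exploratory.
2. **Section 2.9:** delete independent t-tests as an alternative for the three-arm comparison. Use one global three-arm test on the primary endpoint, followed by one named correction for the pairs (Tukey, for example). Naming one pair in advance and testing it alone would serve equally well.
3. **Section 2.9:** report estimates with 95% confidence intervals for all contrasts, whether or not they are significant.
4. **Section 2.9:** correct the printed alpha and state whether tests are two-sided, so that the level of the between-arm test is on record.

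The cost is wording in sections 2.7 and 2.9 and the abstract, with no extra patients, visits or data. The small downside is that no significance claims can be made for the secondary scales or the later time points. If a single pair is named instead of the global test, the other two pairs lose theirs as well.

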**Methods:**

This six-month, naturalistic observational study will involve 105 adult participants (18–65 years) diagnosed with MDD according to DSM-5 criteria. Participants will be categorized to one of three groups: allopathic-only treatment (n=35), ayurvedic-only treatment (n=35), or a combination of both (n=35). Depressive symptom severity will be assessed as primary endpoint using primarily the MDRS, and secondarily HAMD and PHQ-9 scales at baseline, every 2 weeks until week 8, followed by monthly assessments until months 6. Secondary outcomes will exploratively include side effects (UKU, GASE, MARS), quality of life and daily functioning (WHOQoL-BREF, GAF, FAST) as well as general health measures (e.g. lab tests).

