### Study assessments

2.4

All three arms will involve structured assessments at baseline, every 2 weeks until week 8, followed by monthly assessments up to month 6 to measure symptom severity, quality of life, functional capacity, adverse events, and adherence (see **figure 2** for a detailed overview of assessment schedules across all visits). The study will involve a detailed medical history, including sociodemographics, medical and psychiatric history, and previous and current medication. Clinical symptoms related to depression, trauma, and sleep are assessed using the test procedures described below.

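### Depression-scale analysis is left open between unadjusted tests, repeated-measures ANOVA and mixed models on four of nine assessments, with baseline adjustment triggered only by a weak significance test

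*Protocol article*

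**What the plan says.** All references are to the protocol article.

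- **Between-group test.** Section 2.9 states that for continuous outcomes, with depression scale scores as its first example, "Analysis of Variance (ANOVA) or independent samples t-tests will be used to compare means between the three treatment groups". No baseline covariate is named there or elsewhere.
- **Longitudinal models.** The same section continues "Given the repeated measures design (baseline, 8 weeks, 3 months, 6 months" and gives repeated-measures ANOVA and mixed-effects models as examples, with a group-by-time interaction. The abstract (Results) and section 1.2 name the same four time points.
- **Visits.** Section 2.4 schedules "structured assessments at baseline, every 2 weeks until week 8, followed by monthly assessments up to month 6", and the abstract (Methods) gives this schedule for the depression scales. Taking week 8 as month 2, the follow-ups are weeks 2, 4, 6 and 8 and months 3, 4, 5 and 6.
- **Adjustment.** Section 2.9 promises correction for confounders in analyses where the groups differ significantly.
- **Analysis set and missing data.** Section 2.9 announces an intention-to-treat approach and says that ways of dealing with missing data will be considered and documented.
- **Groups.** The abstract gives "allopathic-only treatment (n=35), ayurvedic-only treatment (n=35), or a combination of both (n=35". Allocation is not randomised. Section 2.3 ties arm to hospital, and ties the combined arm to earlier allopathic treatment.

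**The concern.** Section 2.7 puts the emphasis on MADRS at week 8. For that result the plan allows a t-test on observed scores, an ANOVA, a repeated-measures ANOVA or a mixed model. These can give different answers from the same data, and the text does not choose.

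Three things are at stake:

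1. **Baseline severity.** Patients reach their arm by clinical indication, preference and treatment history, so baseline MADRS may well differ between arms. Whether the week-8 comparison allows for this depends on a preliminary significance test.
2. **Precision.** With 35 per arm, dropping a strong predictor is costly. The study expects no difference between arms (sections 1.2 and 2.9), so an imprecise comparison tends to look like confirmation.
3. **Dropout.** Weeks 2, 4 and 6 carry the most information on patients who are missing at week 8, yet they are outside the listed time points. If repeated-measures ANOVA is run on completers, a patient who misses month 6 also drops out of the week-8 result. Treatment may be re-evaluated at week 8, so later visits should not decide who counts at week 8.

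**Working it through.** **Inputs from the article.** Three arms of 35; "a moderate effect size (0.5) (for change in symptoms of depression"; "we achieve a statistical power of >0.8"; baseline plus eight follow-ups scheduled; baseline plus three listed for analysis.

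**Assumed, because the article does not give them.** Correlation ρ between baseline and week-8 MADRS (0.3 to 0.7); SD of 8 at both times; a 3-point baseline gap between two arms; the dropout rates and patterns below.

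**1. The plan's own power figure.** At two-sided α = 0.05, a paired test within one arm (n = 35, d = 0.5) has power 0.82, so the stated figure reproduces as a within-arm test. For two arms of 35 at d = 0.5, power is 0.54 (noncentral t) or 0.55 (normal approximation). The between-arm contrast is therefore the one short of precision. The α printed in section 2.9, "an alpha error probability of 0.5", is a separate matter.

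**2. Visit count.** Eight follow-ups less three listed leaves five unlisted: weeks 2, 4 and 6 and months 4 and 5.

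**3. How often the adjustment trigger fires.** Standardised gap 3/8 = 0.375; noncentrality 0.375 × √(35/2) = 1.57 on 68 degrees of freedom; power at two-sided 0.05 is 0.34. Such a gap would be missed about two times in three.

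**4. What a missed gap does.** With equal SDs and no arm effect given baseline, the week-8 difference is biased by 3ρ and the change-score difference by −3(1 − ρ).

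| ρ | Week-8 score | Change score |
|---|---|---|
| 0.3 | 0.9 | −2.1 |
| 0.5 | 1.5 | −1.5 |
| 0.7 | 2.1 | −0.9 |

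**5. Precision.** Relative to the week-8 score (variance 1), a change score has variance 2(1 − ρ) and a baseline-adjusted analysis 1 − ρ². The saving from adjustment is ρ² against the week-8 score. Against the change score it is 1 − (1 − ρ²)/(2(1 − ρ)) = (1 − ρ)/2. Power is for 35 against 35, d = 0.5, two-sided 0.05, normal approximation.

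| ρ | Saving vs week-8 score | Saving vs change score | 35 per arm is worth, vs week-8 score: 35/(1 − ρ²) | Power: week-8 / change / adjusted |
|---|---|---|---|---|
| 0.3 | 9% | 35% | 38.5 | 0.55 / 0.42 / 0.59 |
| 0.5 | 25% | 25% | 46.7 | 0.55 / 0.55 / 0.68 |
| 0.6 | 36% | 20% | 54.7 | 0.55 / 0.65 / 0.74 |

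**6. Completer repeated-measures ANOVA.** With 5, 10 or 15% missing independently at each of three follow-ups, 35 × 0.95³ = 30.0, 35 × 0.90³ = 25.5 and 35 × 0.85³ = 21.5 patients per arm remain. Independence is the harsh case; if patients drop out for good, the losses overlap and fewer are lost.

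**7. What the unlisted visits add.** Simulation with 1,000 runs per correlation structure (two structures, baseline to week-8 correlation 0.48 and 0.50), 35 against 35, SD 8 and no true effect. Dropout followed high scores in one arm and low scores in the other, a deliberately adverse pattern. About 19% were missing at week 8, and about 33% missed at least one of the four listed points.

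| Analysis of the week-8 contrast | Mean bias, points | SD of estimate |
|---|---|---|
| t-test, observed week 8 | 1.80, 1.51 | 2.07, 2.09 |
| Baseline-adjusted, observed week 8 | 0.75, 0.59 | 1.92, 1.89 |
| Change, completers of four points | 0.13, 0.07 | 2.45, 2.38 |
| Likelihood model, four points, change | 0.65, 0.62 | 2.19, 2.17 |
| Likelihood model, nine points, change | −0.14, 0.04 | 2.16, 2.17 |

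The Monte Carlo error of the means is 0.06 to 0.08. The likelihood models here treat baseline as a response, so the table isolates the effect of the visits; the covariate gain is in step 5. Going from four to nine points hardly changes the SD but removes most of the bias. The completer analysis shows little bias in this setting, but its variance is larger by (2.45/2.16)² − 1 = 29% and (2.38/2.17)² − 1 = 20%.

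**The case against.** The plan is better than a quick reading suggests, and four stronger charges fail.

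- **That the comparison is simply unadjusted.** Section 2.9 does promise correction for confounders where groups differ significantly, and baseline MADRS is an obvious candidate. What stands is that the trigger is weak at this size.
- **That baseline is ignored and only weak models are planned.** Mixed-effects models are named, and in any group-by-time model baseline is one of the time points. What stands is that baseline is never a fixed covariate and no model is chosen.
- **That repeated-measures ANOVA contradicts the intention-to-treat statement.** It is only an example, and missing-data handling is left open, so deletion of incomplete patients is not stated. The completer counts in step 6 are conditional on that reading and on assumed rates.
- **That five unused visits waste a great deal of precision.** They do not. Their benefit is in bias, shown here only under an assumed adverse dropout pattern.

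It can also be said that a protocol article leaves model details to an analysis plan. That is fair for the covariance structure or baseline-by-visit terms. The point here rests on the tests, time points and adjustment rule that the article does state, which an analysis plan following it would inherit. It is also true that section 3.2 concedes confounding and selection bias, and that section 4 calls the findings hypothesis-generating.

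**Conclusion.** The point holds in a limited form. As written, the plan permits a week-8 t-test or a completer repeated-measures ANOVA. Both are less precise than one baseline-adjusted mixed model, and under baseline imbalance or dropout they can be more biased. The rule meant to protect against imbalance would miss an assumed 3-point gap about two times in three, while that gap moves an unadjusted week-8 comparison by 0.9 to 2.1 points. The variance saving from always adjusting is 9 to 36% against the week-8 score and 35 to 20% against a change score, for ρ from 0.3 to 0.6.

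The correlation, SD, gap and dropout are assumptions; the visit count and the wording of the methods are not. This is an improvement that should be made. It does not show that the study will give a wrong answer. In non-randomised groups, adjusted and change-score estimates can differ, and neither is guaranteed to be unbiased.

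**What to change.** In section 2.9, replace t-tests, ANOVA and repeated-measures ANOVA for the scale outcomes with one likelihood-based mixed model on all scheduled visits. It should contain arm, visit, arm-by-visit and the baseline score of the same scale, always included whatever a significance test of baseline differences shows. MADRS comes first, then HAM-D and PHQ-9 in the same way.

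Report two sets of results from it: the week-8 differences between arms, and the change from baseline to week 8 within each arm. The second is the study's directional hypothesis and should not be lost in the rewording. Align the time points listed in the abstract, section 1.2 and section 2.9 with the visit schedule, keeping week 8, month 3 and month 6 as reporting times.

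The cost is wording. The visits are already scheduled and mixed models are already named. Two limits should be stated with the change: the model relies on data being missing at random, and baseline adjustment does not remove confounding by hospital and prior treatment, so the between-arm results remain exploratory.

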### Study intervention

2.3

This study will utilize a naturalistic observational design, leveraging the established expertise and practices of two distinct clinical settings: Nadiad Ayurveda Hospital (for Ayurvedic only and combined treatments) and Shree Krishna Hospital, Department of Psychiatry, Bhaikaka University, Karamsad, Anand (for allopathic treatments). The assignment to the groups follows a clear system. The two hospitals have different areas of focus. One clinic (Shree Krishna Hospital) provides exclusively allopathic treatment, while the other (Nadiad Ayurveda Hospital) provides Ayurvedic treatment. Patients who are treated at the Ayurvedic hospital but have previously received allopathic treatment will continue to receive allopathic treatment (combined therapy). The clinic is selected based on clinical indications and in consultation with the patient.

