### Strengths

3.1

The study design we have developed provides an opportunity to evaluate allopathic, Ayurvedic, and combined therapeutic approaches in a real-world setting. The study also highlights the potential of integration of Ayurvedic and allopathic approaches as innovative approaches with real-world generalizability. The study is designed as a longitudinal study with a follow-up period of six months so that long-term effects can also be exploratively investigated. The study includes extensive clinical and somatic examinations, self-reports, and interviews so that both objective and subjective assessments can be considered. The design allows individualized and adaptive treatment of patients.

The problem of ergodicity (40)—that interindividual differences do not necessarily reflect intraindividual dynamics and that conclusions based on group-level data cannot be directly transferred to individual patients—plays a role in the interpretation of our findings. We explicitly use group-level results as evidence of average treatment effects and will use them as a starting point for individualized care. We operationalize this through measurement-based monitoring, stepwise treatment adaptation, and—where feasible—idiographic designs (e.g., intensive longitudinal assessments, single-case or N-of-1 approaches) to evaluate within-person responses and further optimize treatment for the individual patient.

The study thus offers high ecological validity and the potential to be transferable to everyday clinical practice . At the same time, the collection of routine blood markers and vital parameters offers a opportunity to gain exploratively neurobiological insights. The multi-professional team and international collaboration offer the advantage of combining in-depth expertise in various fields.

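### Arm A is at one hospital and Arms B and C at the other, so every comparison with Arm A, and the overall three-group test, measures treatment and hospital together

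*Protocol article*

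**What the plan says.** Section 2.3 (Study intervention) describes a study "leveraging the established expertise and practices of two distinct clinical settings". It assigns "Nadiad Ayurveda Hospital (for Ayurvedic only and combined treatments") to one and allopathic treatment to the other: "One clinic (Shree Krishna Hospital) provides exclusively allopathic treatment, while the other (Nadiad Ayurveda Hospital) provides Ayurvedic treatment". Arm C is formed inside the Ayurvedic hospital: "Patients who are treated at the Ayurvedic hospital but have previously received allopathic treatment will continue to receive allopathic treatment (combined therapy"). Section 2.1 confirms that there is no randomisation and that this is a setting "where the group assignment reflects patient preference and clinical practice in specialized hospitals".

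For the between-group comparison, section 2.9 states that "Analysis of Variance (ANOVA) or independent samples t-tests will be used to compare means between the three treatment groups", with post-hoc pairwise tests. It adds repeated-measures ANOVA or mixed-effects models for the group-by-time interaction, and effect sizes with 95% confidence intervals for significant findings. No hospital term is named. Correction for confounders is promised where the groups differ significantly. The stated expectation is equality: "We also hypothesize that the groups do not differ in terms of treatment success (between group effect").

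Section 2.7 makes change in depressive severity on the MADRS, especially at week 8, the primary endpoint. Section 3.2 (Limitations) concedes confounding, selection bias and dependence of treatment choice on the treating clinic. It does not say that arm and hospital are inseparable.

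**The concern.** With one hospital on each side, anything that makes MADRS change differ between the hospitals for reasons other than treatment enters the A-versus-B and A-versus-C differences in full. Examples are catchment, the mix of in- and outpatients, the amount of attention, and the way interviews are conducted at later visits. The error term of an ANOVA, a t-test or a patient-level longitudinal model contains only variation between patients within a hospital, so it does not reflect this.

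The p-value then answers whether treatment and hospital together make a difference, while the hypothesis in section 2.9 is about treatment success. The distortion can run either way. A hospital influence can produce a significant difference between equally good treatments, or it can cancel a real difference and appear to confirm the expected equality.

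**Working it through.** **1. The plan's own figure.** Section 2.9 reports power above 0.8 for N = 105 and effect size 0.5, with alpha printed as 0.5 (0.05 is presumably meant). A paired within-group test with standardised change 0.5, n = 35 and two-sided alpha 0.05 has power 0.820, which matches. At the same alpha, a between-group comparison of 35 with 35 at d = 0.5 has power 0.54. The published figure thus fits the within-group hypothesis, which is not a contrast between hospitals and is untouched by this point. None of these calculations allows for a hospital effect.

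**2. Layout (section 2.3).**

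| | Allopathic hospital | Ayurvedic hospital |
|---|---|---|
| Arm A | 35 | 0 |
| Arm B | 0 | 35 |
| Arm C | 0 | 35 |

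An indicator for hospital is identical to an indicator for Arm A. Hospitals within treatment have 0 degrees of freedom on this contrast. The confounder correction in section 2.9 cannot help, because hospital cannot be entered beside the A-versus-B or A-versus-C contrast. A mixed model has the same limit.

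**3. Error rate when treatments do not differ.** Inputs: 35 per arm (Abstract) and two-sided 5%. The intraclass correlation (ICC) is the share of the variance of MADRS *change* that lies between hospitals. The article does not give it, so a range is assumed.

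With total variance 1, the true variance of the A−B difference is (1 − ICC) × 2/35 + 2 × ICC. The patient-level test estimates only the first term. The ratio of true to reported standard error is therefore

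k = sqrt(1 + 35 × ICC / (1 − ICC)),

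and the rejection rate is 2 × P(t₆₈ > t₀.₉₇₅,₆₈ / k). For example, at ICC 0.02, k = sqrt(1 + 0.70/0.98) = 1.31.

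| Assumed ICC for change | k | A vs B (or A vs C) | Three-group ANOVA (200,000 simulations) | B vs C |
|---|---|---|---|---|
| 0 | 1.00 | 5.0% | 5.0% | 5% |
| 0.005 | 1.08 | 7.0% | 6.8% | 5% |
| 0.01 | 1.16 | 9.1% | 8.9% | 5% |
| 0.02 | 1.31 | 13.2% | 13.1% | 5% |
| 0.05 | 1.69 | 24.1% | 24.3% | 5% |

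B versus C stays at 5% because the shared hospital effect cancels in the difference.

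**4. Rater offset.** Suppose raters at one hospital score every MADRS higher by a constant c. In a change score, (week 8 + c) − (baseline + c) = week 8 − baseline, so the offset disappears and the rejection rate stays at 5%. It does not disappear if raw week-8 means are compared. With c = 3 points and an assumed SD of 10 (0.3 SD), A versus B then rejects in 23.6% of studies (noncentral t, 68 degrees of freedom). For the primary endpoint, only an offset or influence that differs between baseline and week 8 matters.

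**The case against.** The strongest reply is that the article already limits itself. Section 3.2 names confounding and the role of the treating clinic, sections 1.2 and 2.7 call the question exploratory, and section 4 calls the findings hypothesis-generating rather than a basis for clinical recommendations. This tempers the consequence, and it stands to that extent. It does not give a reported p-value or interval its nominal meaning for treatment. The explicit causal disclaimer in section 3.2 concerns individual components of treatment, not the separation of treatment from hospital.

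A second reply is that the hospital belongs to the object of study, since section 1.1 presents Ayurveda as a whole system delivered in specialised hospitals. That is a legitimate choice of estimand, but it is the one proposed below and should then be stated.

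A reader might infer more than the article supports in four ways:

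- *The tests will reject far more often than 5%.* This depends on a hospital variance that is not given. There is no inflation at ICC 0 and only a modest amount at 0.005.
- *A few points of stable rater difference would produce false positives on the primary endpoint.* Such an offset cancels in change scores.
- *Section 3.1 claims to have isolated treatment from hospital.* The sentence "We explicitly use group-level results as evidence of average treatment effects" comes from a discussion of group averages versus individual patients. It needs aligning, but it makes no such claim.
- *B versus C is a clean treatment comparison.* It is free of hospital aliasing only. Arm C is defined by previous allopathic treatment (sections 2.3 and 2.3.3), so it remains confounded.

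**Conclusion.** The point holds for A versus B, A versus C and the overall three-group test, whichever of the named models is used. These estimate treatment plus hospital, and no analysis of these data can divide the two. That conclusion follows from section 2.3 alone and needs no assumption.

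The size does need one. If the hospitals do not differ in MADRS change for other reasons, error rate and coverage are nominal. Under assumed ICCs for change of 0.005 to 0.05, the false-positive rate at nominal 5% is 7% to 24%. A non-significant result is equally unable to show that the treatments are equal. The within-group hypothesis is not affected, and B versus C is affected only by its own confounding.

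**What to change.** 1. Section 2.9: define A versus B and A versus C as differences between care at one hospital and care at the other. Do not present their p-values, or a non-significant result, as a test of treatment difference or equality. Apply the same reading to the overall three-group test.
2. Section 3.2: state that arm and hospital are inseparable for these contrasts and that covariate adjustment cannot change this.
3. Abstract conclusions and section 3.1: align the wording on comparative and average treatment effects with items 1 and 2.
4. Identify B versus C as the only within-hospital contrast, and state its confounding by prior allopathic treatment beside it.
5. Optional: show the Arm A intervals also widened by sqrt(1 + 35 × ICC/(1 − ICC)), that is by 1.16, 1.31 and 1.69 at ICC 0.01, 0.02 and 0.05. Label them as resting on assumed values, since the study cannot estimate a hospital variance.

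The PHQ-9 is already planned beside the MADRS, so no further measure is asked for. The cost is a few sentences and no additional data. The downside is a more modest claim for the Arm A contrasts.
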